# A cluster randomized trial to evaluate external support for the implementation of positive behavioral interventions and supports by school personnel

**DOI:** 10.1186/1748-5908-9-12

**Published:** 2014-01-15

**Keywords:** Implementation, Sustainability, Fidelity, Mental health services disparities, Behavioral health, Urban schools, School-wide positive behavioral interventions and supports

## Abstract

**Background:**

Urban schools lag behind non-urban schools in attending to the behavioral health needs of their students. This is especially evident with regard to the level of use of evidence-based interventions with school children. Increased used of evidence-based interventions in urban schools would contribute to reducing mental health services disparities in low-income communities. School-wide positive behavioral interventions and supports (SWPBIS) is a service delivery framework that can be used to deliver universal preventive interventions and evidence-based behavioral health treatments, such as group cognitive behavioral therapy. In this article, we describe our ongoing research on creating internal capacity for program implementation. We also examine the cost-effectiveness and resulting school climate when two different levels of external support are provided to personnel as they implement a two-tier SWPBIS program.

**Methods/Design:**

The study follows six K – 8 schools in the School District of Philadelphia randomly assigned to consultation support or consultation-plus-coaching support. Participants are: approximately 48 leadership team members, 180 school staff and 3,900 students in Tier 1, and 12 counselors, and 306 child participants in Tier 2. Children who meet inclusion criteria for Tier 2 will participate in group cognitive behavioral therapy for externalizing or anxiety disorders. The study has three phases, baseline/training, implementation, and sustainability. We will measure implementation outcomes, service outcomes, child outcomes, and cost.

**Discussion:**

Findings from this study will provide evidence as to the appropriateness of school-wide prevention and treatment service delivery models for addressing services disparities in schools. The effectiveness and cost-effectiveness analyses of the two levels of training and consultation should help urban school districts and policymakers with the planning and deployment of cost-effective strategies for the implementation of evidence-based interventions for some of the most common behavioral health problems in school children.

**Trial registration:**

ClinicalTrials.gov identifier: NCT01941069

## Background

### Services disparities

Several epidemiologic studies have shown that only one in five children with emotional and behavioral disorders receive mental health services [1-3]. Low-income and ethnically diverse children lag well behind their middle class, Caucasian counterparts in rate of service utilization [3,4]. Access barriers, such as lack of specialized services in low-income communities, high cost,and poor service quality, and stigma have been found to affect service utilization by ethnically diverse children [5-9]. Service delivery strategies that address access barriers and minimize the effects of stigma are likely to reduce service disparities [10].

### Schools’ role in reducing mental health disparities

Services provided in school settings are ideal for identifying and supporting children at risk for mental disorders [11] and for advancing the goal of reducing and eliminating services disparities because they are available to all children. Services are offered in convenient, close to home locations, are often provided at little or no cost to the families, and can be provided while the child is attending school [12-14]. School-based services reduce the stigma associated with seeking mental health services [15] and also afford the opportunity to serve children who are at risk for mental disorders [16-18]. As such, schools can play a significant role in addressing mental health services disparities in low-income urban communities [19,20].

### Externalizing and anxiety disorders

Aggressive, defiant, disruptive and antisocial behavior such as the behavior seen in children with, or at risk for, externalizing behavior disorders—*i.e.*, Oppositional Defiant Disorder (ODD), Conduct Disorder (CD)—have a lifetime prevalence of approximately 10% [21,22] and are highly prevalent in school settings [23-25]. These disorders have been found to lead to academic underachievement, grade retention, school suspension and expulsion, and later problems with the law [26-28]. Early onset of aggressive and antisocial behavior in elementary school has been found to be related to a persistent and chronic trajectory of antisocial behavior into middle childhood and adulthood [29,30].

Anxiety disorders—*i.e.*, Generalized Anxiety Disorder (GAD), Social Phobia (SP), Separation Anxiety Disorder (SAD)— affect up to 13% of the child population [31,32]. Anxious children are much more likely than non-anxious children to have problems with social and peer relations [33,34], academic achievement [35], school refusal [36,37] and future socio-emotional adjustment [38,39]. Children with GAD, SAD, and SP share the same underlying construct of anxiety [40,41], evidence a very high comorbidity rate and have been reported to respond similarly to treatment regardless of which disorder is principal [42,43]. Anxiety disorders are highly prevalent among inner city school children [44-46]. Urban children are especially at risk for anxiety because of the deleterious effects of living in unsafe and deprived neighborhoods [47].

### School-wide positive behavioral interventions and supports (SWPBIS)

SWPBIS is an integrated service delivery framework that targets changes in school climate by creating improved systems and procedures [48,49]. The practices and systems of SWPBIS are organized along a three-tiered continuum of prevention with a behavioral theoretical orientation and the empirical foundation of applied behavior analysis (ABA). Primary prevention strategies focus on preventing new cases of problem behaviors by using school-wide (Tier 1, universal) strategies, such as school-wide discipline, classroom behavior management, and effective instructional practices. Emphasis is placed on teaching all students key behavioral expectations and routines and creating a proactive means of communication for students and school staff. Randomized clinical trials have shown that schools employing SWPBIS have demonstrated better school climate (*e.g.*, fewer student disciplinary problems), higher levels of perceived school safety as reported by students and staff, greater reductions in the number of office discipline referrals (ODR), and improved reading scores compared to schools that did not use SWPBIS and/or did not implement SWPBIS with fidelity [48,50-54]. Some SWPBIS programs also offer targeted group-based support for at risk children (Tier 2, secondary prevention) and individualized support for more severe cases (Tier 3, tertiary prevention). In the present study, children who exhibit need for more targeted support will be offered participation in group cognitive behavioral therapy (GCBT) interventions for externalizing behavior problems or anxiety.

### GCBT for externalizing and anxiety problems

The Coping Power Program CPP; [55], a GCBT intervention, has been found to be effective at reducing aggressive behavior, covert delinquent behavior and substance abuse among aggressive boys [56]. Studies using a briefer version of CPP (Anger Coping) also reported significant reductions in aggressive behavior at post-intervention among targeted aggressive boys, compared to untreated aggressive boys and normal controls [57,58]. Another GCBT intervention, Friends for Life FRIENDS; [59], has been proven to be effective for the prevention and treatment of GAD, SAD, and SP [60-63]. For example, in a randomized trial with children diagnosed with an anxiety disorder, 76% of children assigned to FRIENDS were diagnosis free at the end of the 10-week trial compared to 6% of children assigned to a wait-list condition [63].

### Use of school personnel for implementation of evidence-based interventions (EBIs)

A number of recent studies have shown that school personnel can be successfully trained in the development and implementation of SWPBIS [48,50,64] and GCBT for externalizing and anxiety disorders [65-68], respectively. Also, SWPBIS has been successfully implemented in a number of inner city schools around the country [69,70]. Unfortunately, school personnel and school counselors often lack adequate training in the implementation of SWPBIS and other EBIs. In addition, schools in urban settings often do not have adequate funding to contract mental health professionals to provide child services. The present study directly addresses these important barriers by enhancing school capacity to deploy EBIs.

### Theoretical framework

We developed and pilot-tested the program in two K–8 schools that have the same ethnic and socio-economic breakdown as the schools participating in this study. The project was funded by the Centers for Disease Control and Prevention (CDC; RFA-CD-08-001; *Elimination of health disparities through translation research; R18*). The adaptation and testing of the interventions used in the study were organized around the first three steps of the Public Health Model (*i.e.*, Defining the problem; Identifying causes/risk factors; Developing and testing the intervention) See, [71-73] (see Figure 1). Specifically, we collected needs assessment data, assessed symptom profile and mental health service utilization of typical students in the participating schools, investigated risk and protective factors, conducted a review of EBIs for ethnically-diverse children, selected and adapted interventions based on the characteristics of the student population and specific constraints of under-resourced schools, and pilot-tested SWPBIS and EBIs for externalizing behavior problems and anxiety ([name] et. al., Development and implementation of a SWPBIS program with mental health supports in urban schools, submitted) [74]. The present study will extend this work by addressing the fourth step (Implementing the intervention/measuring effectiveness) of the Public Health Model [71]. Outcome measures for the present study were selected based on the implementation framework developed by Proctor and colleagues [75,76], including the assessment of implementation outcomes, service outcomes, and child outcomes (see Figure 1).

**Figure 1 F1:**
[figure not shown]
**Public health model for project development and implementation.** Adapted from Kutash, K., Duchnowski, A. J., & Lynn, N. (2006). School-based mental health: An empirical guide for decision-makers. Tampa, FL: University of South Florida, The Louis de la Parte Florida Mental Health Institute, Department of Child & Family Studies, Research and Training Center for Children’s Mental Health.

### Study aims

The specific aims of the study are:

1. To determine whether program content and process fidelity for Tier 1 (for all students) and Tier 2 (for at risk and high risk students) differ between schools receiving a higher level of support (Consultation plus Coaching, C + C) and schools receiving a lower level of support (Consultation, C) for program implementers.

2. To determine whether school climate, office discipline referrals, and participants’ diagnostic status, symptom and impairment severity, coping skills, and academic productivity differ between schools receiving different levels of support (C or C + C).

3. To assess changes in mental health disparities brought about by Tier 1 (perception of school climate, student suspension rates) and Tier 2 (proportion of students with unmet need), respectively.

4. To determine the incremental cost-effectiveness of SWPBIS C versus SWPBIS C + C.

### Study fit with the funding opportunity

The study is aligned with the funding opportunity *PAR-11-104, Reducing health disparities among minority and underserved children (R01)*, in that it evaluates the comparative effectiveness of two levels of support for school personnel for the implementation of a continuum of mental health prevention strategies for low-income, ethnically diverse children in non-traditional service settings.

## Methods/Design

Six K–8 schools in the School District of Philadelphia were randomly assigned to either Consultation or Consultation plus Coaching (See Figure 2). A stratified random assignment list of schools to condition was generated using a computerized random assignment program [77]. Schools were stratified to group one if their baseline School Climate (CREST) scores were below the median CREST scores or to group two if the CREST scores ≥ the median value. The units of analyses for Tier 1 are all of the students in those K-8 schools (650 per school), leadership team members (eight per school) and other school staff (30 per school). The units of analyses for Tier 2 are the children meeting criteria for inclusion in one of the GCBT groups (enroll a total of 367 students assuming a 17% dropout; approximately 51 eligible students per school), the school counselors (two per school) conducting the GCBT groups, and the groups themselves (14 per school; see Table 1).

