**Tier 1**				
	Students	1,950	1,950	3,900
	Leadership team members	24	24	48
	School staff	90	90	180

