The general analytical approach for testing our hypotheses will be the Laird and Ware mixed effects model [112] and the Generalized Estimating Equation (GEE) approaches [113,114]. Mixed effects and GEE are statistical approaches based on regression techniques for analyzing correlated data collected repeatedly from the same subject. The study design will allow us to examine the between- subjects effect related to the two levels of support, and a within-subjects effect corresponding to time points (five time points), as well as a type of support (C, C + C) by time interaction effect. These analyses will be conducted using SAS Proc Mixed, which utilizes the mixed effects models, and SAS Proc Genmod, which utilizes GEE [115]. Both the mixed effects model and GEE approaches allow estimation of fixed effect parameters such as time, and time by treatment interaction. If the interaction term is significant, it indicates that change in school climate and/or reduction in ODRs over time is significantly different between the two levels of support. If the interaction term is statistically not significant, the changes over time for the two primary outcomes will be presented by the time effect only, which represents both levels of support. The advantage of utilizing these methods is that all information available from each student is used, including variables with missing observations. In the proposed analyses, we will consider students measured within classes are correlated and will be nested within classes. Nested analysis will be chosen as part of Proc Mixed and Proc GEE, as such, the intraclass ‘intracluster’ correlation (ICC) will be part of the overall variance covariance matrix.

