Changes from pre- to post- implementation in diagnostic status, symptom severity and impairment level, coping skills and academic productivity during Implementation across all schools, regardless of level of support, will be analyzed using McNemar tests. For each of the listed primary outcomes, a series of 2X2 tables will be constructed to test changes from pre- to post- in the pertinent categories using McNemar tests. Alpha level will be adjusted to 0.025 based on Bonferroni criteria for multiple comparisons. We will also use McNemar tests to test the hypothesis that the pre- to post- level of improvement in diagnostic status, symptom severity, impairment level, coping, and academic productivity obtained during Implementation will be maintained during Sustainability among schools receiving C + C.

We would like to determine whether pre- to post- improvement in diagnostic status, symptom severity, impairment level, and academic productivity differ by support condition during the implementation phase. In addressing this research question, and for the sake of simplifying the statistical analysis, each student will be categorized as either improved or not improved based on change from pre- to post-. A category one will be assigned if a student’s diagnostic status, for example, changes either from positive to intermediate, intermediate to negative, or positive to negative. Otherwise a score of zero will be assigned. Similar coding will be used for symptom severity, coping, impairment level, and academic productivity. We will use chi-squared tests to compare the proportion of (yes/no) for each of the primary outcomes between C and C + C type of supports. To examine changes in the rate of ODRs between baseline and follow up during each school year, the number of students with at least one ODR will be defined at baseline and at the follow up and a 95% confidence interval for such changes will be constructed for each of the five years.

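### Six schools were randomised within median-split climate strata that cannot balance at 3 v 3, yet the plain chi-squared tests fixed for Tier 2 improvement cannot account for the stratum.

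*Protocol article*

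**What the plan says.** Under Methods/Design, six K–8 "schools in the School District of Philadelphia were randomly assigned to either Consultation or Consultation plus Coaching". On the method: "A stratified random assignment list of schools to condition was generated using a computerized random assignment program". The strata are defined by baseline climate: "Schools were stratified to group one if their baseline School Climate (CREST) scores were below the median CREST scores". The remaining schools, those scoring at the median or higher, form the second stratum. No block size or within-stratum ratio is stated.

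The article does not say outright how many schools are in each arm, but Table 1 together with the per-school figures in Methods/Design implies three in each.

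The Data analytic plan compares the arms in two ways:

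- School climate and office discipline referrals go into mixed models and GEE, which "allow estimation of fixed effect parameters such as time, and time by treatment interaction".
- Tier 2 children are each coded as improved or not improved from pre to post on diagnostic status, symptom severity, coping, impairment and academic productivity. C is then compared with C + C: "We will use chi-squared tests to compare the proportion of (yes/no) for each of the primary outcomes".

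The McNemar tests and the aim three tests compare time points, not arms. No analysis in the article names the CREST stratum or the baseline CREST score.

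**The concern.** A factor used to restrict randomisation normally reappears in the between-arm analysis, because the sponsor thought it prognostic enough to stratify on. The need is stronger when the strata cannot be split evenly between the arms, because arm and stratum are then correlated in the data actually obtained.

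If children in low-climate schools improve at a different rate from children in high-climate schools, part of that difference will be read as an effect of support level. Diagnostic status, which the sample size section names as the primary outcome, is among the variables tested this way.

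**Working it through.** **1. Schools per arm.** Table 1 arm totals divided by the per-school figures in Methods/Design:

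- students, Tier 1: 1,950/650 = 3
- leadership team members: 24/8 = 3
- school staff: 90/30 = 3
- students, Tier 2: 153/51 = 3

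All four agree on 3 v 3.

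**2. Strata.** Six distinct scores cut at their own median give three schools below it and three at or above it.

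**3. Possible allocations.** There are C(6,3) = 20 ways to choose three schools for one arm. The number that put k low-climate schools in that arm is C(3,k) × C(3,3−k):

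| k | 0 | 1 | 2 | 3 |
|---|---|---|---|---|
| allocations | 1 | 9 | 9 | 1 |

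So 18 allocations are 2:1 in one stratum and 1:2 in the other, two are 3:0, and none is balanced. The exception is a tie: if only the third and fourth scores are equal, the strata hold 2 and 4 schools, and C(2,1) × C(4,2) = 12 of the 20 allocations balance exactly.

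**4. How a stratum difference reaches the chi-squared test.** Let the proportion improved be p_L in low-climate and p_H in high-climate schools, with no effect of support and equal numbers per school (the plan's 51). With a 2:1/1:2 split:

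- arm with two low schools: (2p_L + p_H)/3
- other arm: (p_L + 2p_H)/3
- difference: (p_L − p_H)/3

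One third of the stratum difference appears as an arm difference. Within each stratum the arms have the same proportion, so a stratum-adjusted comparison gives zero. Under a 3:0 split the whole difference would appear, and arm could not be separated from stratum.

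**5. Price of adjusting, for an analysis at school level.**

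- Correlation of arm with stratum: (2×2 − 1×1)/9 = 1/3
- Variance factor: 1/(1 − 1/9) = 1.125
- Residual degrees of freedom: 6 − 2 = 4 falls to 6 − 3 = 3, so the 5% two-sided t value rises from 2.776 to 3.182
- Break-even: 1 − 1/[(3.182/2.776)² × 1.125] = 0.32

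Precision improves only if the stratum explains roughly a third or more of the between-school variance.

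**6. The longitudinal models.** The contrast tested there is support by time. In balanced data it rests on each unit's change from year one. A stratum main effect is the same at every time point, so it cancels from the change and leaves the contrast where it was. Only a stratum-by-time (or baseline-CREST-by-time) term can move it.

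**The case against.** **Covariates may be left to the SAP.** This stands for the mixed models and GEE. The sentence on their fixed effects gives examples only, so silence about the stratum there is no finding. It does not stand for the chi-squared tests: the article selects them expressly, to keep the analysis simple, and a plain 2×2 test has no place for a stratum.

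**A starting gap in climate is already handled.** This largely stands. Climate is measured from year one, which is baseline and one of the five time points, so a constant gap falls into the support main effect and not into the tested interaction. Regression to the mean and stratum-specific trends are not covered.

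**Nothing links climate to Tier 2 improvement.** This stands, and it is why no size can be given. The chi-squared tests concern children's diagnosis, symptoms and functioning, not climate.

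**Stronger readings that the article does not support.** A reader might infer that leaving out the stratum makes the arms start unequal. It cannot: any inequality comes from the allocation. Unequal stratum counts are certain without ties, but unequal mean climate is not. Scores 1, 2, 3, 4, 5, 7 split as {1, 3, 7} and {2, 4, 5} sum to 11 in each arm. Stratifying also helped on average. For six simulated normal school scores the mean absolute gap between arms is 0.57 between-school SD with the strata, against 0.65 SD for unrestricted 3 v 3 allocation.

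In the same simulation the arm with two high-climate schools starts 0.47 SD higher on average, and is the higher arm in 81% of draws. That is an expected starting gap under an assumed normal distribution, not a bias in any planned contrast. Nor does the article say that CREST is the questionnaire used for the climate outcome. The label makes that plausible, but it remains an inference.

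**Conclusion.** The point holds for the Tier 2 comparison of C with C + C, and it is a modest one. Unless CREST scores tie at the median, one arm holds at least two of the three low-climate schools, and the chosen test cannot allow for this. Any low-versus-high difference in improvement would then be partly attributed to support level: one third of it under a 2:1/1:2 split with equal school sizes.

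This describes the allocation actually obtained. If each allocation and its mirror image were equally likely, chance decided which arm received the extra low-climate school, so no systematic advantage to either arm is implied. The magnitude is unknown, because it depends on CREST values and on a link between climate and improvement that the article does not give.

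That children are analysed individually although schools were randomised is a separate and larger matter, which the article partly acknowledges under Challenges and limitations.

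**What to change.** In the Data analytic plan, replace the plain chi-squared tests of improvement between C and C + C with a stratum-adjusted comparison, and report the unadjusted result beside it. A Cochran-Mantel-Haenszel test stratified by CREST group is the simplest form, but it deals with the stratum only. A logistic or GEE model with a stratum term can also respect the school clusters. State the realised split of each stratum: a 3:0 split would rule out adjustment for the stratum, and a balanced 2/4 split would largely remove the need.

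If the mixed models and GEE are adjusted as well, specify stratum by time or baseline CREST by time, since a main effect alone leaves the tested contrast unchanged.

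The cost is a change of wording, using baseline scores already held. Where the analysis is at school level, it takes one of four residual degrees of freedom and improves precision only if the stratum explains about a third or more of the between-school variance. That uncertainty is the reason to show both results.
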